| Interventions: | The examined intervention is a non-contrast cranial syngo DynaCT Sine Spin scan with an ARTIS Icono angiography system.  The intervention itself takes under 1 minute. The timespan from enrolment to the last investigation specific visit (the non-contrast syngo DynaCT Sine Spin) is 4 hours at max. |
| Control: | The control intervention is a non-contrast cranial MDCT (at least 64 slice) |
| Number of subjects with rationale: | The existing literature clearly documents MDCT as the gold standard for the detection of acute, spontaneous intracranial hemorrhage.^19^ Therefore the readings of the MDCT will be set as ground truth.  To calculate the sample size, hypothetical experiments were simulated. To account for variation, the diagnostic performance of hypothetical readers was varied around 99% for the sensitivity and around 98% for specificity. Rates were attributed randomly with equal chance. To represent “difficult cases”, i.e. patients who present with an isolated infratentorial hemorrhage we introduced a subpopulation of patients for whom the performance of raters was only 70% sensitivity. This subset was weighted in the final sample size calculations with 2 %.  Each sample size, n_i=1,..,19_ = 80,…,260 was evaluated by sampling 999 times n_i_ individual samples with a range of readers from 1 to 7.  If power is set at 90%, the number of readers at 6, and the drop-out rate at 5%, a total of **252 patients (**238 patients without drop-outs) must be recruited. The patients must be pre-selected in a ratio of hemorrhage positive to hemorrhage negative of 1:1, i.e., 126 patients are presenting with and 126 patients without intracranial hemorrhage. To ensure an enrollment in this ratio, a bucket design will be used. There will be three predefined buckets: (1) 126 acute ischemic (non-hemorrhagic) stroke patients, (2) 126 hemorrhagic stroke patients, which include (3) 14 patients with an isolated infratentorial or basal hemorrhage. |
| Duration of the investigation: | 36 months total  24 months enrollment period |
| Investigation schedule: | 25. October 2022: first patient-in (anticipated)  31. December 2024: last patient-out (anticipated) |
| Investigator(s): | [name]. [name]. (PI)  [name] [name], M.D. (Co-PI and US Chair) |
| Investigational site(s) | Multicentric (up to 30 sites)  Up to 30 sites in Switzerland, United States of America, France, Finland and Spain |

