# 6. CLINICAL INVESTIGATION DESIGN

## 6.1 General clinical investigation design and justification of design

The clinical investigation is designed as a cross-sectional, non-inferiority trial with prospective open label data collection and blinded endpoint assessment. The intervention to be studied is non-contrast syngo DynaCT Sine Spin. The intervention will be done as in standard of care setting.

The patient population consists of patients with a suspected severe acute ischemic stroke (NIHSS at admission ≥ 7 and time from last seen well maximum 24 hours) or with symptoms suggestive of an intracranial haemorrhage (for example reduced consciousness). All patients will undergo first non-contrast MDCT imaging and then afterwards non-contrast syngo DynaCT Sine Spin imaging. As the study is designed to be cross-sectional, there is no control group. All patients will undergo the same procedures. Only patients in whom no invasive intervention is planned between both scans and in whom it is feasible to perform both scans within a time-period of up to four hours can be enrolled. This time span however is assumed to be far shorter in many patients (especially in mothership patients; most likely under 30 minutes). The total duration of the intervention itself will be 7 seconds scan time and up to 1 minute procedure time (not including positioning of the patient). Patient positioning is done independently from the participation in the proposed clinical investigation. The total duration of the clinical investigation for each patient will be up to four hours from enrolment to the last assessment. There is no further follow-up visit planed after the sine-spin non-contrast FDCT.

Patients will be enrolled after the non-contrast MDCT and best medical therapy. This approach was chosen as enrolment prior to the non-contrast MDCT, and best medical therapy would lead to inacceptable time delays in this patient cohort. Based on clinical symptoms and imaging findings of the non-contrast MDCT patients can be enrolled in one of three buckets: (1) acute ischemic stroke patients, (2) patients with an intracranial haemorrhage which has supratentorial portions and (3) isolated infratentorial or basal intracranial haemorrhages (including perimesencephalic SAH). In total 252 patients will be enrolled (for justification of sample size see section 11) and they are distributed over the buckets in the following proportions:

- Bucket 1 (acute ischemic stroke patients) 126 patients

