- Bucket 2 and 3 (haemorrhage patients) 126 patients including 14 patients in bucket 3 (isolated infratentorial or basal intracranial haemorrhage including perimesencephalic SAH)

Local investigators must keep a screening log.

The primary objective (sensitivity and specificity of non-contrast syngo DynaCT Sine Spin imaging for the detection of intracranial haemorrhage) will be assessed by blinded readers in an imaging core-lab. All readers will be blinded to all clinical characteristics and will not be involved in the treatment or enrolment of patients. Prior to the core-lab assessment all scans will be anonymized, reconstructed in a standardised way (fixed angles and slide sizes) and randomized. All readings will be noted on standardized forms.

The ground truth (i.e., if an intracranial haemorrhage is present or not) will be defined based only on the MDCT scans according to the following procedure: If the reading of the clinical reader (the enrolling physician at the participating site) and the reader from the first blinded core-lab (provided by the Neurovascular Imaging Research Core, [name], University of California LA, Los Angeles, California, USA) is consistent this will be deemed as ground truth. If they are inconsistent a second core-lab (provided by [name], Inselspital Bern, Bern, Switzerland) will make a final ruling (majority vote). The second core-lab can use all available clinical information but will be blinded to the results of the reading from core lab one. The following table illustrates the definition of the ground truth:

| Modality | Reader | Analysis |
| --- | --- | --- |
| MDCT | Clinical Reader | Agreement: ground truth |
|  | Core-Lab 1 | Disagreement: Unblinded expert reader in 2^nd^ corelab determines ground truth (majority vote) |

Table 1: Definition of the ground truth

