2. Although patients will be enrolled based mainly on clinical features, we defined a required number of patients (n = 14) with bleedings which are according to current literature harder to detect on predecessor FDCT generations than on MDCT, i.e. isolated bleedings in the posterior fossa / isolated infratentorial hemorrhages.^39, 48^ This approach was chosen to estimate the diagnostic performance of non-contrast syngo DynaCT Sine Spin imaging also in challenging, rare cases. It therefore allows a broader estimate of its ability for the detection and exclusion of intracranial hemorrhages. However, for the final analysis these cases will have a lower weight as they would have if they were count in by their proportion (14 isolated infratentorial bleedings out of 126 bleeding cases: 11%). In the final analysis they will contribute to the estimate of the sensitivity for the detection of intracranial hemorrhage of FDCT with a fixed weight of 2% (please refer to section 11.5 for a detailed description of the primary analysis). This weight which is lower than their share within the sample size was chosen as from the principal investigators and the US chairs clinical experience (including over 30 years of attending work in neuroradiology/neurosurgery) these cases are very rare (< 1%) in the investigated population and rarely present with symptoms, which would lead to a direct to angiography approach. To further validate their estimated prevalence in the patient group of question (patients with symptoms suggestive of an acute ischemic stroke), we did an analysis of all suspected stroke cases presenting to the University Hospital Basel in the years 2015 to 2019. The data was derived from the Swiss Stroke Registry and included 5,448 patients. Out of these only 48 patients (0.8%) presented with an isolated infratentorial bleeding.

The decision to include 14 isolated infratentorial / posterior fossa bleedings was chosen to be able to generate meaningful data for this bleeding type as well. It assumes that the sensitivity for the detection of these bleedings is 70%. In this case we would have a power of 80% to show that the lower bound of the corresponding 95%-CI interval of the sensitivity for these cases is above 50%. Please refer to section 11 for a detailed description of the calculation of the sample size.

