## 9.2 Assessments of outcomes

All outcomes will be assessed by a blinded and independent imaging core-lab. For this purpose, all scans will be anonymized, reconstructed in a standardized matter (i.e. fixed slice thickness 5 mm, distance 3 mm and angles - orbitomeatal) and randomized prior to evaluation.

The main core-lab will be provided by the Neurovascular Imaging Research Core at UCLA ([name], University of California Los Angeles, Los Angeles, California, USA). The experience of the Neurovascular Imaging Research Core at UCLA as an imaging and angiography core lab is unrivaled, including more than 15,000 acute ischemic stroke cases treated with endovascular therapies in the last several years.

To ensure compliance with the Protocol and adequate acquisition technique of the FDCT and MDCT at the respective site the first five cases from each site will be deemed as lead-in cases. Cases can be excluded and deemed as Screen Failures if they show clear evidence of (a) operator failure (for example due to clear artifacts due to objects in the field of view, wrong positioning of head, wrong acquisition protocol, severe motion artifacts, missing reconstructions) or (b) technical failure due to missing calibration of the scanner. The ultimate decision to exclude cases is made by the Independent Core Lab (under the supervision of [name]). In such a case it is the obligation of the Sponsor to perform retraining. Excluded cases will be replaced to ensure adequate power.

The imaging core-lab will use a standardized form to note all endpoints, in specific:

- Primary outcome:
  - Occurrence of an intracranial hemorrhage (yes/no)

The primary outcome will be assessed on both scans.

Only on the MDCT scans the following variables will be assessed as well:

- - Type of intracranial hemorrhage (SAH, intraparenchymal hemorrhage, intraventricular hemorrhage, subdural hemorrhage, epidural hemorrhage)
  - Is the intracranial hemorrhage isolated to the infratentorial region? (yes/no)

Only on the FDCT scans the following variables will be assessed as well:

- - Was contrast-media present at the evaluation of the scan? (yes/no)
  - If yes, did it enhance your capability to detect/exclude a hemorrhage? (yes/no)

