## 11.2 Determination of Sample Size

To calculate the sample size, hypothetical experiments were simulated. We estimate a sensitivity of 99% and a specificity of 98% of non-contrast syngo DynaCT Sine Spin imaging for the detection of intracranial hemorrhage as it was described for the predecessor generation in the literature.^48^ To account for variation, diagnostic performance of hypothetical readers was varied with rates of 98.5%, 99% and 99.5% for sensitivity and 97.5%, 98% and 98.5% for specificity. Rates were attributed randomly with equal chance.

Sensitivities and specificities of readers were generated from correlated binary random variables. To reproduce the correlated readings between readers, a high correlation between binary random variables was chosen. This assumption was made based on the literature and judgement of the principal investigators. We further simulated lower correlations which showed consistently that an approach using a high correlation is more conservative (i.e., leading to a higher sample size). Generated outcomes were vectors with 1 (true positive) and 0 (false negative) for sensitivity and 1 (true negative) and 0 (false positive) for specificity. The quotient of the occurrences of 1 and the number of cases with/or without a bleeding being sensitivity and specificity, respectively. In case sensitivity or specificity was 100%, a false negative (for sensitivity) and a false positive (for specificity) was introduced into the generated output. This enabled to still fit a model (see below).

To represent “difficult cases”, i.e. patients who present with an isolated infratentorial intracranial hemorrhage, we introduced a subpopulation of patients for whom the performance of raters was only 70% sensitivity. We chose n = 14 patients based on an additional sample size calculation. With this subsample, there is an 80% chance (power) that the lower bound of the 95%-CI of a sensitivity of 70% is higher than 50%. However, we assume that the subsample substantially overrepresents the incidence of difficult cases in the study population (see section 6.1). Therefore, we attributed a lower weight in the model to each difficult case.

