### 11.5.3 Secondary Analysis

Fleiss’ kappa will be estimated to assess interrater reliability between 6 readers. Specificity, accuracy, positive predictive value, and negative predictive value will be calculated for FDCT.

For the subset of patients with an isolated infratentorial hemorrhage the sensitivity of FDCT for its detection including its 95%-CI will be reported separately.

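### Bucket 3 is recruited as infratentorial or basal bleeds, but the 2% weight, the core-lab item and the separate subset cover infratentorial bleeds only, and no variable is named to assign the weight

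*Protocol*

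**What the plan says.** **Recruitment.** Section 6.1 defines the third bucket as "3) isolated infratentorial or basal intracranial haemorrhages (including perimesencephalic SAH") and sets its size at "14 patients in bucket 3 (isolated infratentorial or basal intracranial haemorrhage including perimesencephalic SAH"). The synopsis agrees: "14 patients with an isolated infratentorial or basal hemorrhage". Bucket 2 in section 6.1 takes hemorrhages with supratentorial portions.

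**Everything after recruitment.** Later in section 6.1 the same 14 patients are described as "isolated bleedings in the posterior fossa / isolated infratentorial hemorrhages", and their unweighted share is given as "14 isolated infratentorial bleedings out of 126 bleeding cases: 11"%. The registry count offered in support of a low weight, 48 of 5,448, is of isolated infratentorial bleeds. Section 11.2 defines difficult cases as "patients who present with an isolated infratentorial intracranial hemorrhage, we introduced a subpopulation of patients", assigns them 70% sensitivity, and sizes the group at 14 for 80% power to show a lower bound above 50%. Section 11.5.3 reports separately: "For the subset of patients with an isolated infratentorial hemorrhage the sensitivity of FDCT". The core-lab MDCT form in section 9.2 asks "Is the intracranial hemorrhage isolated to the infratentorial region? (yes/no"). It also records hemorrhage type, including SAH, but has no item for a basal location.

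**The weight.** Section 11.5.2 gives difficult cases a weight of 2% and names no variable that identifies them. Two candidates exist: the hemorrhage location that the site enters at enrollment (synopsis, measurements and procedures) and the core-lab item. Section 1.8 lets core-lab results overrule site assessments.

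**The concern.** The protocol treats the 14 patients recruited and the 14 patients weighted as one group, but defines them differently. A basal bleed can count toward bucket 3 and still fall outside the difficult-case definition. Two things then depend on which definition is applied.

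The first is the primary sensitivity. The weight enters that estimate directly, and the success rule requires its lower confidence bound to exceed 95%. The second is the infratentorial subset. Its stated 80% power assumes 14 infratentorial cases, and every basal bleed counted toward bucket 3 takes one of those places.

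**Working it through.** **Inputs.** 126 hemorrhage patients, 14 of them in bucket 3 (6.1). Total weight of difficult cases 0.02; 238 patients without drop-outs; 70% sensitivity in difficult cases and 99% otherwise (11.2). Let k be the number of bucket 3 bleeds that the core lab does not rate isolated infratentorial. The protocol gives no value for k and no detection rate for basal bleeds, so both are assumptions below.

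**The plan's own figure.** 14/126 = 11.1%, which reproduces the stated 11%.

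**Weight per patient.**
- If the weight follows the bucket: 0.02/14 = 0.143% for each of the 14, and 0.98/112 = 0.875% for each other bleed. The ratio is 6.1.
- If it follows the core-lab item, each of the k cases joins the ordinary group and carries 0.98/(112 + k):

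| k | Weight of each such case | Ratio to 0.143% |
|---|---|---|
| 1 | 0.867% | 6.1 |
| 3 | 0.852% | 6.0 |
| 5 | 0.838% | 5.9 |
| 7 | 0.824% | 5.8 |
| 13 | 0.784% | 5.5 |

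With 238/2 = 119 hemorrhage patients the denominator is 105 + k, and the ratio runs from 6.5 (k = 1) to 5.8 (k = 13).

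**Expected weighted sensitivity.** The planning value is 0.98 × 0.99 + 0.02 × 0.70 = 98.42%. Let s be the detection rate of the k cases.
- Core-lab rule: 0.98 × (112 × 0.99 + k × s)/(112 + k) + 0.02 × 0.70.
- Bucket rule: 0.98 × 0.99 + 0.02 × [(14 − k) × 0.70 + k × s]/14.

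| k | s = 70%, bucket | s = 70%, core lab | s = 99%, bucket | s = 99%, core lab |
|---|---|---|---|---|
| 3 | 98.4% | 97.7% | 98.5% | 98.4% |
| 5 | 98.4% | 97.2% | 98.6% | 98.4% |
| 7 | 98.4% | 96.7% | 98.7% | 98.4% |

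At s = 99% the core-lab rule leaves the planning value unchanged, and the two rules differ by at most 0.3 points for these k. At s = 70% they differ by 0.7, 1.2 and 1.7 points. These are weighted means of rates. The primary analysis uses the fixed-effect intercept of a logit random-effects model, so they show direction and rough size, not the model estimate.

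**The subset.** If only infratentorial bleeds count, it holds 14 − k patients: 11, 9 or 7 for k = 3, 5 or 7. The protocol does not state its reader correlation, so the 80% cannot be reproduced exactly. A beta-binomial approximation (six readers, logit Wald bound) with assumed within-patient correlations of 0.10 and 0.15 gives 84% and 78% power for 14 patients, which makes the stated 80% plausible. The same approximation gives 67% and 60% for 9 patients, and 56% and 49% for 7.

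**The case against.** The strongest reply is that the two definitions may nearly coincide. Bucket 2 takes bleeds with supratentorial portions, so a bucket 3 basal bleed should have none, and the core lab could answer yes for it. A perimesencephalic SAH could be answered either way. This is a fair reading and may keep k small. It does not settle the matter, because section 6.1 lists basal bleeds beside infratentorial ones as an alternative, and no instruction tells the core lab how to classify them.

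A reader might infer that basal bleeds will receive six times their intended weight. The documents do not support that. It would need basal bleeds to be enrolled, the core lab to answer no, and the weight to follow the core-lab item. If the bucket decides, all 14 share the 2%. If infratentorial only is the intent, which the registry count and section 11.2 suggest, ordinary weight for a basal bleed is correct.

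A reader might also infer a definite loss of sensitivity. That rests on giving basal bleeds the 70% rate that section 11.2 states for infratentorial bleeds only.

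It can also be said that naming a weighting variable belongs in the SAP, and that the site records location before the FDCT exists. Both points have force, and nothing shows that the choice would be made with the readings in view. But the conflict is in recruitment and data collection. A SAP cannot supply a blinded basal-location item that the form does not collect, and section 11 requires the SAP only before database closure, which does not guarantee that it precedes the FDCT readings.

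**Conclusion.** The contradiction stands. Bucket 3 admits basal bleeds, while the weight, the 70% rate, the power statement, the core-lab item and the reported subset are written for infratentorial bleeds. The protocol leaves open which patients carry the 2% weight in the primary sensitivity.

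For a patient on whom the two definitions disagree, the weight differs about six-fold; this is arithmetic and needs no assumption about detection. The effect on the estimate is conditional: negligible if such bleeds are detected at 99%, and about 0.7 to 1.7 points for 3 to 7 cases if they are detected at 70%. If infratentorial only is the intended definition, the weighting is sound and the fault lies in the bucket, which can close short of the 14 cases that the subset's power requires. One of the two must be corrected on either reading.

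**What to change.** Use one definition for the bucket 3 count, the 2% weight and the separate sensitivity, in one of two ways:

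- Add a blinded core-lab MDCT item asking whether the hemorrhage is isolated infratentorial or basal, including perimesencephalic SAH (yes/no), and apply it to all three.
- Keep the infratentorial definition, and count only those bleeds toward the 14.

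In either case, name the weighting variable in section 11.5.2 before any FDCT scan is read. The cost is at most one form item, with matching wording in the synopsis and sections 6.1, 9.2, 11.2 and 11.5. No extra readers are needed and the planned sample size does not change. Under the second option bucket 3 may fill more slowly.

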### 9.2.1 Assessment of primary outcome

The primary outcome “occurrence of intracranial hemorrhage” will be assessed by an independent blinded core-lab as detailed in 9.2

### 9.2.2 Assessment of secondary outcomes

See above under 9.2

### 9.2.3 Assessment of other outcomes of interest

There are no other outcomes of interest.

### 9.2.4 Assessment of safety outcomes

All AEs up to 24 hours after the procedure are investigated and documented in the source document. They are collected in the appropriate eCRF if they are deemed to be related to the procedure.

#### 9.2.4.1 Adverse events

All AEs, which are deemed to be procedure related by the local PI and occur during the conduct of the clinical investigation and/or within 24 hours of the intervention or till discharge (whatever happens earlier) of the subject are collected and documented on an ongoing basis. Due to the nature of the intervention, there are no foreseeable AEs

#### 9.2.4.2 Laboratory parameters

Not applicable

#### 9.2.4.3 Vital signs

Not applicable

### 9.2.5 Assessments in subjects who prematurely stop the clinical investigation

As there is only one visit, there is no foreseeable scenario in which a subject might prematurely stop the clinical investigation.

### 9.2.6 Follow-up of the subjects after the regular termination of the clinical investigation

No follow-up is planned.

## 9.3 Procedures at each visit

### 9.3.1 Visit 0 – Screening and enrollment

Stroke severity will be evaluated using the NIHSS in the emergency room. All subjects undergo a non-contrast MDCT scan (and CT angiography/perfusion if clinically indicated) immediately after admission. This MDCT scan will be done completely independently from the study as part of normal clinical routine. For clarification the MDCT scan could have been done at an external hospital (in case of transfer patients) provided the images were transferred to the PACS of the enrolling centre prior to enrolment and the enrolling physician has ensured adequate quality of the external MDCT scan.

Basic medical and surgical patient history will be obtained in all subjects according to local standard practice and in accordance with the AHA/ASA guidelines on stroke^44^ including medication, laboratory tests and vital signs. Women in childbearing age will be tested for pregnancy (study specific). A basic physical examination including NIHSS assessment will be performed. Intravenous thrombolysis should be administered immediately if the patient is deemed to be eligible under the international AHA/ASA guidelines^44^ and according to local standard practice. We highly recommend not to intubate the patient between the MDCT and FDCT scan.

Thereafter the subject will be screened for inclusion and exclusion criteria. All these subjects will be entered into the screening log (e.g., age, NIHSS, disapproved diagnosis). If the investigator comes to the decision that the subject qualifies for a trial participation, informed consent must be obtained immediately. If the investigator in agreement with the treating physician decides the subject is not able to give informed consent an independent physician has immediately to be organized. The independent physician must confirm or disapprove the trial participation for the specific subject.

*See Appendix C- US Protocol Amendments

